#### Cost-effectiveness analysis

The incremental cost-effectiveness ratio (ICER) is calculated as the difference in cost divided by the difference in QALYs for the immediate start choir group compared to the wait-list control group:$$ \mathrm{ICER}\kern0.5em  = \left({\mathrm{C}}_{\mathrm{i}}\kern0.5em \hbox{--} \kern0.75em {\mathrm{C}}_{\mathrm{c}}\right)\ /\ \left({\mathrm{E}}_{\mathrm{i}}\kern0.5em \hbox{--}\ {\mathrm{E}}_{\mathrm{c}}\right) $$

Where C = cost measured in dollars

E = effectiveness measured in QALYs

i = the intervention (immediate start choir) group

c = the wait-list control group

The ICER is the cost per QALY resulting from the program, and can be compared to other interventions. Interventions are typically considered to be reasonable if the cost per QALY is $50,000 - $100,000 or less.

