## Method/design

### Overall study design

The Community of Voices study is a multi-site, cluster randomized trial, located in San Francisco, CA (study enrollment from February 2012 – August 2015). Twelve AoA- supported senior centers were randomized to receive the 12-month Community of Voices choir program immediately (intervention group) or after a 6-month delay (wait-list control group). Adults age 60 or older were recruited from the geographic service areas of each senior center. Recruitment and enrollment were conducted in staggered pairs of centers. We completed a comprehensive battery of outcome measures, including cognitive, physical, and psychosocial outcomes hypothesized to be mechanistically related to choral singing. We assessed primary and secondary outcomes for all participants at baseline, 6 and 12 months. Thus, for those in the control group, the study lasted 18 months (6 month wait period, 12- month choir). The main randomized comparison will be at 6 months. The 12-month assessment allows us to examine within-person change over the 12- month period of the choir.

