### Intervention: community of voices choir program

The Community of Voices (Comunidad de Voces in Spanish) choir program was designed specifically with the goal of promoting health and well-being of diverse, community-dwelling older adults. Details about the choir intervention are reported in a separate manuscript. Here, we briefly summarize the intervention.

The program was designed using a translational research approach [33] that incorporated information from evidence-based research on the benefits of singing for older adults, community best practices related to community choirs for older adults, input from experts in delivering choral programs in community settings, and the perspective of senior center directors. The literature was summarized in the introduction. The San Francisco Community Music Center helped design the program. The PI observed an older adult choir directed by the music center and discussed the development with music professionals at the center. Other best practices were considered, such as the older adult choirs that the PI observed during her research in Finland on choral singing [21].

The program was designed to be led by professional choir conductors and accompanists. Professional musicians, some of whom were bilingual, were used to help assure a high level of standardization of program elements [25]. The music center staff was responsible for helping hire, train, and supervise the choir conductors and accompanists. The conductors and accompanists completed training on program components before beginning the choir, and refresher training was conducted as needed.

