#### Choir cost

For each choir, we collected all costs related to personnel (i.e., choir conductor and accompanist salaries), supplies (e.g., music binders, file box for music, piano purchase), and services (e.g., piano tuning). We also included the cost of providing snacks during the sessions.

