#### Health care utilization

We tracked utilization of health care services using a modified measure from the Chronic Disease Self-Management study [59]. Every three months, we assessed visits to a doctor, mental health provider (e.g., counselor, psychologist), other health providers (e.g., home health nurse, physical therapist), emergency room visits and hospitalizations (including number of nights hospitalized and reason for stay), and outpatient surgeries over the past 3 months. The cost per unit of utilization (hospital days) was obtained from the Medical Expenditures Panel Survey and applied to the number of units used to obtain healthcare costs.

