### Statistical analysis plan

Descriptive analyses will estimate means and proportions, measures of variability, and confidence intervals of all measures. When defensible and part of the best available analysis strategy, observed distributions may prompt normalizing transformations. We will determine whether participant baseline characteristics are independent of intervention group assignment (randomization check) and attrition (attrition analysis). Case-wise deletion and other ad hoc approaches to handling missing data will not be used for analysis because they rely on relatively strong assumptions and entail a loss of statistical power. Instead, multiple imputation will allow models to be fit to all available data and will invoke the relatively mild assumption that the data are *missing at random*, conditional on modeled variables [60–63].

Primary analyses will include fitting regression models of continuous participant outcomes. The data has a 3-level structure (centers, participants, repeated measures), which will be accommodated with linear mixed models, including random intercepts both for centers and participants. The main study end-point will be the 6-month assessment. The modeled primary outcomes include the baseline and 6-month assessments of the primary physical, emotional, and cognitive variables (see Table 2). Each outcome will be regressed onto indicators of intervention group assignment and categorical time, as well as the group-by-time interaction. Significant intervention group main effects at 6-months and group-by-time interaction effects would be interpreted and described.

Secondary analyses include models of secondary outcomes that are conceptually similar to the models described above. We will also examine within-group comparisons of 6- and 12-month outcomes to determine any added benefits of extended choral activity and compare the effect of choral participation in the intervention group to that observed in the original control group after choral group participation is offered to them. We will also explore potential intervention effect moderators by fitting models that include key interaction terms; primarily, our focus will be on interactions between experimental group with participant sex, age, and race/ethnicity. The longitudinal models described above will be refit with the inclusion of 3-way interactions (e.g., experimental group-by-sex-by-time).

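### A bare ICER beside an 'or less' benchmark cannot separate good from bad results, and the listed program costs are narrower than the program described

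*Protocol article*

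**What the plan says.** The Study aims section names cost-effectiveness in QALYs as the second of two main aims. The section Cost-effectiveness analysis defines the ICER as follows: it "is calculated as the difference in cost divided by the difference in QALYs for the immediate start choir group compared to the wait-list control group". The only guide to reading it is: "Interventions are typically considered to be reasonable if the cost per QALY is $50,000 - $100,000 or less". Nothing is said about a negative ratio or a negative QALY difference.

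On program cost, the section Choir cost states that "we collected all costs related to personnel (i.e., choir conductor and accompanist salaries"; it then adds supplies (a piano purchase among them), services and snacks. The intervention section says: "The music center staff was responsible for helping hire, train, and supervise the choir conductors and accompanists". It also describes training before the choirs start, refresher training, and a music-center role in keeping implementation consistent.

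On health care, several kinds of use are recorded every three months, but "The cost per unit of utilization (hospital days) was obtained from the Medical Expenditures Panel Survey".

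On timing, Overall study design says "The main randomized comparison will be at 6 months", and the Statistical analysis plan section says "The main study end-point will be the 6-month assessment". The wait-list centers then receive the choir: "for those in the control group, the study lasted 18 months (6 month wait period, 12- month choir". The cost-effectiveness section does not repeat the 6-month window.

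**The concern.** A cost-per-QALY threshold read as a ceiling makes sense only when the program costs more and yields more QALYs. Elsewhere the ratio misleads. It is negative both when the program is dominated (costlier, worse) and when it is dominant (cheaper, better). When the program is cheaper but worse, it is positive and can be small. If the QALY difference is small relative to its standard error, an estimate in one of these quadrants is a realistic prospect.

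The second issue is what goes into the numerator. The article undertakes to cost the program, including the choirs themselves, but the itemized personnel cost leaves out staff work that it describes as part of delivery. The article also calls the program relatively low in cost and suited to wide adoption, so a center planning to copy it would want those inputs counted. What is at stake is the reading of a main aim; the three primary clinical outcomes are unaffected.

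**Working it through.** **Plan figures.** The article gives no cost, QALY or ICER value to reproduce. Its one recomputable figure, the minimum detectable difference of 0.37, supplies the design effect used below.
- Analyzed per arm: 350 × 0.9 / 2 = 157.5. Per center: 350 × 0.9 / 12 = 26.25.
- Design effect: 1 + (26.25 − 1) × 0.015 = 1.379.
- Minimum detectable difference: (1.960 + 0.842) × √(2 × 1.379 / 157.5) = 0.3707, which agrees with 0.37.

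**What the ratio can and cannot show.** ICER = ΔC/ΔE. Net monetary benefit (NMB) = λ·ΔE − ΔC, with λ the value per QALY. The differences are illustrative.

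| ΔC | ΔE (QALY) | ICER | At or below $50,000? | NMB at $50,000 | NMB at $100,000 |
|---|---|---|---|---|---|
| +$500 | −0.01 | −$50,000 | yes | −$1,000 | −$1,500 |
| −$500 | +0.01 | −$50,000 | yes | +$1,000 | +$1,500 |
| −$100 | −0.01 | +$10,000 | yes | −$400 | −$900 |
| +$500 | +0.002 | +$250,000 | no | −$400 | −$300 |

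Rows 1 and 2 share one ICER and have opposite meanings. Row 3 falls under the benchmark with a negative NMB. NMB separates all of them.

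**Could the QALY difference come out negative by chance?** Assumptions, none from the article: EQ-5D SD 0.20, correlation of 0.6 between baseline and 6 months, true 6-month gain 0.02, and the article's ICC of 0.015 applied to EQ-5D.
- SE of the group difference at one time point: 0.20 × √(4 × 1.379 / 315) = 0.0265.
- QALYs over half a year by trapezoid: 0.25 × (baseline difference + 6-month difference). True gain: 0.25 × 0.02 = 0.005.
- Unadjusted SE: 0.25 × √(2 × 0.0265² × 1.6) = 0.0118. P(negative) = Φ(−0.005/0.0118) ≈ 34%. For true gains of 0.01 to 0.03 it runs from 42% to 26%.
- Baseline-adjusted SE: 0.25 × 0.0265 × 0.8 = 0.0053. P(negative) ≈ 17%.

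**Cost items side by side.**
- Personnel: what is counted is introduced by *i.e.*, which closes the list at conductors and accompanists. Supplies and services are introduced by *e.g.*, which leaves those lists open.
- Described as program delivery but without a cost line: music-center hiring, initial and refresher training, supervision and implementation oversight.
- Health-care use recorded: physician, mental-health and other-provider visits, emergency visits, hospital stays and outpatient surgery. Unit named as costed: hospital days.
- The article gives no hours or pay for the missing items, so they cannot be sized.

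**Why the window is worth restating.** Assume utility rises linearly to u = 0.02 at 6 months and then holds, that controls follow the same path 6 months later, and that incremental cost is $300.
- Months 0–6: ΔE = 0.25 × 0.02 = 0.005; ICER = $300 / 0.005 = $60,000.
- Months 0–12: ΔE = (0.75 − 0.25) × 0.02 = 0.010; ICER = $300 / 0.010 = $30,000.

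The two windows fall on either side of $50,000.

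**The case against.** The strongest reply is that the benchmark sentence is background. It reports what is typically considered reasonable and sets no pass/fail test. The article also describes the ICER as the cost per QALY resulting from the program, which presupposes a gain, and a competent analyst would state the quadrant. This stands in part. A reader might infer that the plan would call a costlier, worse program reasonable, but the text does not say so. What remains is that the section offers no other yardstick, and the one it offers is uninformative in three of the four quadrants.

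A reader might also infer that the comparison has no time limit and so takes in the controls' own choir year. The overall design and the analysis section both fix the randomized comparison at 6 months, and immediate start versus wait-list is a contrast of that period. Six months is the natural reading; it is only not restated for costs and QALYs.

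A further inference would be that QALYs are to be compared without baseline adjustment. The article gives the textbook ICER definition and does not exclude adjustment, a detail usually left to the full analysis plan. Restricted randomization also limits center imbalance. Under randomization an unadjusted difference is imprecise, not biased in expectation. The 34% above therefore reflects sampling error under assumed inputs, and 17% remains after adjustment.

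On costs, the reply is that the open services list could hold music-center work and that the wider promise to cost the program could cover it. That is possible, and the hospital-days parenthesis may be only an example. Neither resolves the mismatch in the text.

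**Conclusion.** The point holds on two counts, both resting on stated text. First, a bare ICER beside an 'or less' benchmark cannot distinguish a dominated from a dominant result and can favor a cheaper-but-worse one. This is algebra and needs no assumption; only the dollar and QALY values in the table are illustrative. Second, the itemized personnel and health-care costs are narrower than the program and the utilization that the article describes.

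The size of the omitted cost is unknown. It would be tempting to conclude that the ICER is biased toward a cheaper program, but the article does not establish that: charging start-up items such as a piano to a short horizon pushes cost the other way. The missing window and baseline adjustment are clarifications, not errors. The change is worth making because it concerns a main aim and costs little.

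**What to change.** - Report incremental net monetary benefit at $50,000 and $100,000 per QALY, with an interval that respects center clustering, such as a center-level bootstrap. State the quadrant with any ICER.
- Add music-center hiring, training, refresher training and supervision time to program cost, or state why it is excluded. State how start-up items are charged.
- Reconcile the Choir cost and Health care utilization sections with the program as described, and name the unit cost for each kind of use collected.
- Restate in the cost-effectiveness section that costs and QALYs both cover months 0 to 6, with choir cost for those same months.
- Adjust incremental QALYs for baseline EQ-5D, as a gain in precision. Under the assumptions above the SE falls from 0.0118 to 0.0053.

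The cost is analysis wording, a little extra computation and retrieval of training and supervision hours from the music center. The stated program cost would probably rise somewhat.

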### Statistical analysis plan

Descriptive analyses will estimate means and proportions, measures of variability, and confidence intervals of all measures. When defensible and part of the best available analysis strategy, observed distributions may prompt normalizing transformations. We will determine whether participant baseline characteristics are independent of intervention group assignment (randomization check) and attrition (attrition analysis). Case-wise deletion and other ad hoc approaches to handling missing data will not be used for analysis because they rely on relatively strong assumptions and entail a loss of statistical power. Instead, multiple imputation will allow models to be fit to all available data and will invoke the relatively mild assumption that the data are *missing at random*, conditional on modeled variables [60–63].

Primary analyses will include fitting regression models of continuous participant outcomes. The data has a 3-level structure (centers, participants, repeated measures), which will be accommodated with linear mixed models, including random intercepts both for centers and participants. The main study end-point will be the 6-month assessment. The modeled primary outcomes include the baseline and 6-month assessments of the primary physical, emotional, and cognitive variables (see Table 2). Each outcome will be regressed onto indicators of intervention group assignment and categorical time, as well as the group-by-time interaction. Significant intervention group main effects at 6-months and group-by-time interaction effects would be interpreted and described.

Secondary analyses include models of secondary outcomes that are conceptually similar to the models described above. We will also examine within-group comparisons of 6- and 12-month outcomes to determine any added benefits of extended choral activity and compare the effect of choral participation in the intervention group to that observed in the original control group after choral group participation is offered to them. We will also explore potential intervention effect moderators by fitting models that include key interaction terms; primarily, our focus will be on interactions between experimental group with participant sex, age, and race/ethnicity. The longitudinal models described above will be refit with the inclusion of 3-way interactions (e.g., experimental group-by-sex-by-time).

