### Cluster randomization

Because of the small number of centers involved, simple random assignment of centers to the immediate and delayed start groups could fail to establish equivalent experimental groups at baseline. Therefore, we used restricted randomization (described below) to help ensure balance of center characteristics across experimental groups [32]. We collected data from senior center reports that described the characteristics of each center, including individual-level variables, center-level variables, and readiness for the intervention (Table 1). These variables were used to aid the selection of two matched groups of centers, with each group containing six centers. An algorithm generated all possible partitions of centers into two groups of six centers (462 possible partitions), estimated the profile of center characteristics for each group, and calculated the sum of squared profile differences across groups within each partition. We examined 23 (top 5 %) candidate partitions with the smallest sum of squared profile differences and selected one partition based upon visual inspection of the group-specific profiles. Because recruitment was conducted within staggered pairs of centers, six pairs of centers were created, and each pair included one center from each group. Finally, one group of six centers was randomized to the immediate start group and the other set to the wait-list control group. When recruitment was completed within a staggered pair of senior centers, the randomization assignment was revealed to the corresponding study staff, senior centers, and participants.

**Table 1 Tab1:** Variables used in the restricted randomization process

Level	Variables
Individual level	% needing translation services
	% living alone
	% functionally impaired
	% with “low” income
	% with medical insurance
	% on social security income
	% with nutrition risk
	% age < 60
	% age 60-74
	% age 75-84
	% age 85+
	% African American
	% Asian/Pacific Islander
	% Latino
	% White
	% male
Center level	Whether the following types of activities are offered:
	• cognitive
	• emotional
	• singing
	• arts/crafts
	• health promotion
	• meal service
	• social services
	• transportation services
	• parties/cultural events
	• day trips
Readiness for intervention	Moderately, quite, or extremely

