#### Sample size calculations and power

We aimed to recruit 350 participants, approximately 30 from each of 12 senior centers. Assumptions included intention-to-treat analyses, 80 % power, two-tailed alpha = 0.05, 90 % retention at 6 months, unit-standardized continuous outcomes, and a linear mixed model of group differences at 6 months. Based upon published data from a study involving older adults who completed a year-long choir program [25], the largest intra-cluster correlation (ICC) for any outcome equaled 0.015. Accounting for ICC, cluster size, and attrition, the minimum detectable group difference, *d*, equaled 0.37, which compares favorably to effect sizes based upon the results reported by Cohen and colleagues [25]: overall health rating (0.41); depression (0.38); number of weekly activities (0.57 and 0.77).

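### The random effects named for the primary model cancel out of the group-by-time test, so that test ignores center clustering of change and is anti-conservative if centers differ in 6-month change

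*Protocol article*

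**What the plan says.** Under Cluster randomization, two sets of centers are formed, "with each group containing six centers", and one set is allocated to start the choir immediately.

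Under Statistical analysis plan, the data are described as having three levels (center, participant, repeated measure), "which will be accommodated with linear mixed models, including random intercepts both for centers and participants". The fixed part is stated as follows: "Each outcome will be regressed onto indicators of intervention group assignment and categorical time, as well as the group-by-time interaction". Two time points enter: "The modeled primary outcomes include the baseline and 6-month assessments". Two treatment effects are to be read from the fit: "Significant intervention group main effects at 6-months and group-by-time interaction effects would be interpreted and described". No center-by-time term or center-specific slope is named. Models for the secondary outcomes are to be conceptually similar.

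Under Sample size calculations and power: "We aimed to recruit 350 participants, approximately 30 from each of 12 senior centers", with "80 % power, two-tailed alpha = 0.05, 90 % retention at 6 months", and "the largest intra-cluster correlation (ICC) for any outcome equaled 0.015". The target there is the group difference at 6 months, with a minimum detectable d of 0.37.

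**The concern.** Treatment is allocated to centers, so every treatment contrast needs a standard error that reflects variation between centers. A random intercept for center represents a center difference that is the same at baseline and at 6 months. It removes that stable difference from a comparison of changes, but it cannot represent centers moving apart over the 6 months. The participant intercept cancels in the same way. What remains in the interaction's standard error is residual variance divided by the number of participants, as if participants had been individually randomized.

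It is plausible that centers change by different amounts. Musical style was chosen per choir and repertoire was refined after each choir started. Centers were recruited in staggered pairs, so calendar period differs between pairs. Unblinded staff assessed participants at the centers. If such variation exists, p-values for the interaction are too small and its confidence intervals too narrow, for each primary outcome and again in the secondary models built the same way.

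**Working it through.** **Inputs from the article.** 12 centers, 6 per arm; 350 recruited; 90% retention; two-sided alpha 0.05; 80% power; ICC 0.015; outcomes with SD 1; two time points.

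**Inputs not in the article (assumed).** The within-person correlation r between baseline and 6 months, and the fraction f of the 0.015 center variance that varies over time. I read 0.015 as an ICC of outcome levels; the article does not say whether it refers to levels or change.

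**1. The plan's own figure.** Completers per arm: 350 × 0.9 / 2 = 157.5. Completers per center: m = 350 × 0.9 / 12 = 26.25. Design effect: 1 + (26.25 − 1) × 0.015 = 1.379. Minimum detectable d = (1.960 + 0.842) × √(2 × 1.379 / 157.5) = 0.371. The stated 0.37 reproduces, so the sample size allows for clustering in the 6-month difference.

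**2. What the stated model does to the interaction.** For participant j in center i at time t, write the outcome as fixed effects + center intercept + participant intercept + residual. The change from baseline to 6 months is then fixed effects + difference of two residuals, because both intercepts subtract out. In balanced data the interaction is the difference in mean change, tested with the pooled variance of about 315 individual changes.

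**3. What happens if centers differ in change.** The time-varying center variance is 0.015 × f and the within-center residual variance is 0.985 × (1 − r). Then

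- ICC of change = 0.015f / [0.015f + 0.985(1 − r)]
- variance ratio DE = 1 + (m − 1) × ICC of change
- actual type I error = 2 × [1 − Φ(1.96 / √DE)]

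Example, r = 0.6, f = 0.5: 0.0075 / (0.0075 + 0.394) = 0.0187; DE = 1 + 25.25 × 0.0187 = 1.472; 1.96 / √1.472 = 1.615; error = 10.6%.

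| f | r = 0.4 | r = 0.6 | r = 0.8 |
|---|---|---|---|
| 0 | 5.0% | 5.0% | 5.0% |
| 1/5 | 6.5% | 7.3% | 9.5% |
| 1/3 | 7.5% | 8.8% | 12.4% |
| 1/2 | 8.8% | 10.6% | 15.8% |
| 1 | 12.4% | 15.8% | 24.0% |

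If 0.015 is instead taken directly as the ICC of change, DE = 1.379 and the error is 9.5%.

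**4. Simulation.** Null trials with 12 centers × 26 completers and r = 0.6 gave 5.0% with no center-by-time variance, 8.4% at 0.005, 10.9% at 0.0075 and 15.5% at 0.015, in line with the r = 0.6 column. A test on center-mean changes with 10 df (12 − 2) stayed near 5% throughout.

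**5. The other treatment effect.** The 6-month group contrast from the same random-intercept model keeps the center variance. Simulated with ICC 0.015, r from 0.5 to 0.8 and f from 0 to 1, its error was 5.6–7.2% with normal quantiles and 3.2–4.4% with t on 10 df.

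**The case against.** The strongest reply is that the main comparison is the 6-month difference. The overall design section says so, power is computed for it, and the center intercept does enter it. This stands: the sample-size section never claims to power the interaction, and the contrast it does power is close to nominal. It does not rescue the interaction, which the article lists alongside the 6-month effect as something to be interpreted.

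A second reply is that the word *including* names terms without excluding others, that this is a condensed article, and that an analysis plan may add more. Degrees-of-freedom methods are indeed normally left to such a plan, and their absence is no fault here. But the article does choose to state the random effects of its primary model, and those named are insufficient for one of its two tests.

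Third, the inflation could be smaller. Only the immediate-start centers run a choir during the randomized 6 months, so variation caused by the choirs themselves would sit in one arm. At r = 0.6, simulation then gives 6.9%, 8.2% and 10.7% for time-varying variance of 0.005, 0.0075 and 0.015. A manual and fidelity checks also aim to limit it. This is fair for choir-driven variation. Calendar period and unblinded on-site assessment can affect both arms.

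A reader might infer that type I error simply is 9–19%. The article does not support that. Nothing in it fixes the ICC of change or r; 5% is possible; and 19% at r = 0.6 needs a center-by-time variance of 0.02, above the largest ICC the plan reports. Nor does it say that each center has its own conductor, so that cannot be cited as the cause.

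**Conclusion.** The point holds in limited form: as written, the group-by-time test ignores clustering of change by center, and it keeps its 5% level only if centers do not differ in 6-month change.

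At an assumed within-person correlation of 0.6 and about 26 completers per center, the error is 5% if none of the 0.015 varies over time, about 8–11% if one-third to one-half does, and about 16% if all does. The last case is extreme, since it leaves no stable differences between centers serving distinct populations. When one-fifth to all of it varies, the range is about 6–13% at correlation 0.4 and about 10–24% at 0.8.

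These are rates per test. They are not familywise rates across the three primary outcomes, and they should not be carried over to the 6-month group contrast.

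**What to change.** Either add a random center-by-time effect to the primary model, or analyze the 6-month outcome adjusted for baseline with a center random effect. In both cases, test the treatment contrast on between-center degrees of freedom (Kenward-Roger, or about 10 from 12 centers minus 2), and use the same structure for the secondary-outcome models.

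This takes a sentence of specification and no new data. The article says longitudinal data will not be examined until all sites finish the randomized 6 months, so a change made before then is made without sight of the results.

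The cost is wider confidence intervals and somewhat lower power. As a guide, replacing normal with t quantiles on 10 df in the plan's own calculation gives (2.228 + 0.879) × √(2 × 1.379 / 157.5) = 0.41 as the minimum detectable difference, against 0.37.

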We ascertained serious medical conditions by asking whether they had a current serious medical or mental health condition that might limit their ability to take part in the assessments or weekly choir. We excluded those with self-reported current (but not prior) severe medical or mental health conditions. We asked whether they had plans to move out of the area within 12 months; and if so, they were not eligible. We asked if they had regularly sung in a choir in the past 6 months, and excluded those who reported singing weekly (those singing less than weekly or not at all were eligible).

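### Fitted with a single residual variance, the participant random intercept bases the standard error of the 6-month group difference on the average of the baseline and 6-month variances; a visit-specific covariance would avoid this at almost no cost

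*Protocol article*

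**What the plan says.** The Statistical analysis plan section makes the 6-month assessment the main end-point. Both visits enter the model as outcomes: "The modeled primary outcomes include the baseline and 6-month assessments of the primary physical, emotional, and cognitive variables". The fixed effects are also given: "Each outcome will be regressed onto indicators of intervention group assignment and categorical time, as well as the group-by-time interaction". Dependence between repeated scores and within centers is handled by mixed models, "which will be accommodated with linear mixed models, including random intercepts both for centers and participants". Two kinds of effect are to be read from the fit: "Significant intervention group main effects at 6-months and group-by-time interaction effects would be interpreted and described".

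The section does not state the residual variance structure. It does allow that "observed distributions may prompt normalizing transformations". Secondary outcomes are to be modeled along similar lines. No section gives an SD for any outcome at either visit. The sample size section works with outcomes scaled to unit SD.

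**The concern.** With two visits, a participant random intercept plus one common residual variance is compound symmetry: equal variance at baseline and at 6 months. The group difference at 6 months is a contrast at one visit, and its precision depends on the variance at that visit. If the two variances differ, the model takes part of that precision from baseline. A larger spread at 6 months makes the test too liberal. A smaller spread makes the confidence interval too wide and costs power.

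The article does not justify equal spread, and there are reasons why it might fail in either direction. Two primary outcomes are completion times (Trail Making B minus A, and five chair stands), where spread can move with the mean. The third, the PHQ-8, has a floor. The baseline sample is also selected. The Screening measures section says "We excluded those with self-reported current (but not prior) severe medical or mental health conditions", and it also screens on dementia diagnosis and word recall. Such selection could relax over six months. These are possibilities, not facts reported in the article.

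**Working it through.** **Inputs.** From the article: "We aimed to recruit 350 participants, approximately 30 from each of 12 senior centers"; two groups, "each group containing six centers"; 90% retention, ICC 0.015, two-sided alpha 0.05, 80% power and unit SD (Sample size calculations and power). Assumed, because the article gives no SDs: k = SD at 6 months / SD at baseline, shown from 0.80 to 1.25.

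**The plan's own figure.** N = 350 × 0.9 = 315, or 315/12 = 26.25 per center. The design effect is 1 + 25.25 × 0.015 = 1.379. The detectable difference is (1.960 + 0.842) × 2 × √(1.379/315) = 0.371, which reproduces the stated 0.37. That figure uses a single unit SD, so the present point does not touch it.

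**Where the average comes from.** Let v0 and v6 be the visit variances and c their covariance. Write s = (y0 + y6)/√2 and d = (y6 − y0)/√2. Then Var(s) = (v0 + v6)/2 + c and Var(d) = (v0 + v6)/2 − c. A random-intercept model with one residual variance estimates these two quantities and treats s and d as uncorrelated. Since y6 = (s + d)/√2, the model assigns it variance [Var(s) + Var(d)]/2 = (v0 + v6)/2. The omitted term is Cov(s, d) = (v6 − v0)/2, which is zero only when the variances are equal.

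For balanced (or imputed) data with equal arms, and leaving clustering aside:

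- squared SE used = 2(v0 + v6)/N
- true squared SE = 4·v6/N
- ratio of SEs: q = √[(1 + k²)/(2k²)]
- type I error = 2Φ(−1.96·q)

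| k | (1 + k²)/(2k²) | q | 1.96·q | Type I error |
|---|---|---|---|---|
| 0.80 | 1.281 | 1.132 | 2.218 | 2.7% |
| 0.90 | 1.117 | 1.057 | 2.072 | 3.8% |
| 1.00 | 1.000 | 1.000 | 1.960 | 5.0% |
| 1.10 | 0.913 | 0.956 | 1.873 | 6.1% |
| 1.25 | 0.820 | 0.906 | 1.775 | 7.6% |

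**Power when k is below 1.** Take a contrast that would have 80% power with the 6-month variance (true effect 2.802 standard errors). Power becomes Φ(2.802 − 2.072) = 77% at k = 0.90 and Φ(2.802 − 2.218) = 72% at k = 0.80.

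**Check with clustering.** A simulation used 12 centers of 26, ICC 0.015, visit correlation 0.5 or 0.7, a z test and 20,000 runs per setting. It gave about 3.1%, 4.3%, 5.5%, 6.6% and 8.2% at the five values of k. Using only the 6-month variance gave about 5.6% at every k. The absolute level depends on the reference distribution, which the article does not state. With t on 10 degrees of freedom the averaged-variance test ran from about 1.5% at k = 0.80, through 3.0% at k = 1.00, to 4.9% at k = 1.25. In both cases the rate drifts with k.

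**Group-by-time.** With two visits this effect is √2 times the group difference in d, and Var(d) is estimated directly from within-person change. In the same simulation its type I error stayed at 5.1% to 5.6% for every k.

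**The case against.** The strongest reply is that the article does not fix the model criticized here. It says that the mixed models include random intercepts, which is not an exhaustive description, and visit-specific residual variances are compatible with it. A condensed article may leave the residual structure to a full analysis plan. That stands against the stronger reading, which a reader might infer, that the plan imposes a common variance and therefore has a wrong error rate. The documents support neither half: the residual structure is unstated, and with equal SDs the test is nominal.

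Further parts of the reply also stand:

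- The effect is modest for SD ratios near 1, at 3.8% to 6.1% for k from 0.9 to 1.1. Nothing in the article points to a ratio outside that range. Screening sets no cut-off on any of the three primary outcome measures.
- A choir effect that pushes PHQ-8 scores toward the floor cannot produce a type I error, because the null is then false. It would also act in one arm only before month 6. It bears on interval width and power alone.
- The power loss is relative to the better analysis, not to the planned 80%. If the planning SD of 1 is read as the baseline SD and the raw difference is held at 0.37, power at k = 0.90 is Φ(2.802/0.90 − 2.072) = 85%, and at k = 0.80 it is Φ(2.802/0.80 − 2.218) = 90%, even with the averaged variance.
- One of the two effects to be interpreted, group-by-time, is essentially unaffected.

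Two parts do not carry. Optional normalizing transformations address shape and need not equalize variances across visits. Multiple imputation fills in scores but does not change the covariance of the model fitted to them. The article is also not silent on covariance: it names a device for the repeated-measures level, and the ordinary fit of that device has this property.

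**Conclusion.** The point holds as a conditional one. If the participant random intercept is fitted with one residual variance, the 6-month group difference takes its standard error from the average of the two visit variances. For assumed SD ratios from 0.80 to 1.25 the nominal 5% test then runs from 2.7% to 7.6%. There is no error at equal SDs, and the direction cannot be known from the documents. These figures rest on complete or imputed data, equal arms, a normal reference distribution and no clustering in the closed form.

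The result for group-by-time concerns unequal visit variances only. Whether change over time varies between centers is a separate question. The sample size calculation is not challenged. This is a minor improvement that costs almost nothing, and no error has been shown.

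**What to change.** In the models of baseline and 6-month scores, for primary and secondary outcomes, specify a visit-specific (unstructured) participant-level covariance in place of the random intercept with homoscedastic residuals. Keep the center random effects. State that the 6-month group difference uses the 6-month variance.

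This is one sentence in the analysis plan. The participant-level covariance goes from two parameters (intercept and residual variance) to three (two variances and a covariance), with about 315 participants expected at 6 months. No new data are needed. If the SDs turn out equal, almost nothing is lost. If the full plan already specifies visit-specific variances, it is enough to say so.
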